## Abstract

**Background:**

Patient-reported outcomes (PRO) are used to measure the effectiveness of interventions for management of chronic conditions such as chronic obstructive pulmonary disease. Many of these instruments require respondents to describe the change in their health status from baseline to a follow-up assessment and poor recall of previous health status often limits the usefulness and validity of these PRO measures. The use of technology has recently increased in PRO measurement. This study aims to mitigate the problems of poor recall by evaluating different strategies as a way to improve the validity of recall of health status among adults with COPD.

**Methods:**

A pilot randomised controlled trial of three strategies to improve patient recall will be tested in an acute care clinical environment. The first strategy is the use of tablet computer technology’s audio-visual facility, the second strategy is the provision of base line PRO responses prior to patients completing their follow-up questionnaires and third is standard practice of completing a questionnaire independently of previous responses. The feasibility of conducting this study in a busy clinical environment will be ascertained using the NIHR criteria for assessing feasibility.

**Discussion:**

There is variability in a person’s ability to recall past events. With studies utilising patient-reported outcome measurement, it has become critically important to develop strategies and ways of supporting the patient to be more accurate recalling their health status. The adaptation of various technological features within mobile devices may provide an opportunity in clinical research studies to improve patient recall of their health status.

**Trial registration:**

ANZCTR12618001605280.

**Electronic supplementary material:**

The online version of this article (10.1186/s40814-019-0475-9) contains supplementary material, which is available to authorized users.

## Introduction

### Background and rationale

Chronic obstructive pulmonary disease (COPD) is a chronic illness that is known to cause significant disability and impair quality of life [1]. Patient-reported outcome (PRO) instruments, such as health-related quality of life questionnaires, are often used in COPD clinical trials [2]. The performance of these instruments is often described as having validity, reliability and responsiveness. Validity is deemed when an instrument or questionnaire contains a set of questions that accurately measures the phenomena such as quality of life. This validity is usually established through three stages; content validity, criterion validity and construct validity [3]. Whereas, reliability, often termed as reproducibility, occurs when an instrument repeatedly provides the same results in different patients with the same stable disease [4]. The responsiveness of a questionnaire is based on its ability to detect change over time, even if these changes are small [3]. The responsiveness of a questionnaire may be inadvertently affected when patients are required to respond to a questionnaire by self-report at different time points and rely on their memory of the experience or symptoms that have occurred [5].

The use of PRO instruments in clinical trials often requires the participant to respond (self-report) to questionnaires about subjective components of their health status at baseline and again at follow-up assessments. Recall of previous information and/or an experience is an important element in the successful utilisation of these PRO instruments in clinical trials [6]. However, patients’ recall is often imperfect. Recall problems fall into two types: random errors in recall and recall bias (p197) [7]. It has been acknowledged that people have varying ability to recall information. People with COPD are often over 50 years of age and the ability to accurately recall information appears to decline with age [8, 9]. In addition, people who have both anxiety and depression have been found to have impaired ability to accurately recall information [10]. Anxiety and depression more commonly occurs in people with COPD [1] and these comorbid conditions may affect the accuracy in recalling information or events [11] .

Recall bias is potentially important as it can affect the validity of a study [6, 11]. Recall bias occurs when participants in the study’s intervention arm may be questioned several times over a period of time about specific aspects of their condition [12]. For instance, a study that is evaluating a technique to improve the symptoms of COPD, patients may be asked about their breathlessness as part of an 8-week pulmonary rehabilitation intervention where they can observe themselves being able to complete physical activities more easily over time. In contrast, the participants in the control arm of the study are asked questions about their breathlessness at the beginning and end of the study. The control group receive usual care in between these data collection time points and the ability to recall any improvement may be reduced without a prompt to do so [12].

In addition to biased recall, errors in recall may also occur. People who complete questionnaires about their physical activity have been found to misreport and/or misinterpret questions [13]. Self-reported data acquired from questionnaires completed by people with impaired physical ability have been shown to be less reliable than those from fully fit people [11]. In the Adventist Health Study, participants’ recalling (self-reported) body weight underestimated the actual body weight [13]. Strategies to limit the impact of impaired recall have included the comparison of completed patient questionnaires with objective measurements [14] such as lung function, six-minute walk test and physical activity completed by patients and verified by observers.

To reduce poor recall, a potential strategy could be, at a subsequent data collection interval, to provide participants with access to their previously completed questionnaire responses. This strategy seeks to anchor [5] participants to their baseline responses during the completion of the questionnaire at a follow-up appointment to aid recall. More recently, various forms of technology have been used in the completion of patient-reported outcome instruments. Telemonitoring [15], web-based platforms [16], touch screens linked to electronic health records [17] and mobile applications [15] all form technology-based mechanisms for patients to engage in self-reporting aspects of their health through the inputting of their responses to specific questions. Therefore, a second strategy could be developed using tablet technology to improve patient recall. To our knowledge, the use of tablet technology’s audio-visual facility has not been utilised to enhance patient recall in the self-reporting of health status through visual and sound recognition from baseline to follow-up time intervals.

### Objectives and hypothesis

Our proposed research seeks to mitigate the problems of poor recall by piloting three different strategies concurrently and to assess the feasibility of these strategies in a busy hospital clinical environment. The first strategy is to evaluate the use of tablet computer technology’s audio-visual functionality as a way to improve the validity of recall of health status among trial participants with COPD. The method involves making an audio-visual recording of the participant’s initial responses to a quality of life questionnaire. Participants will be able to see their image and reflect on how they look at the baseline, and listen to how they sound prior to completing the follow-up questionnaires. This audio-visual recording will act as frame of reference and as an anchor to their past health status to aid their memory. The second strategy is the provision of access to the patient’s previous completed baseline questionnaire prior to completing their follow-up questionnaire. The third strategy is current practice of completing quality of life questionnaires independent of previous responses.

Specifically, we are seeking to understand among patients with COPD undergoing pulmonary rehabilitation, what is the change that occurs in patient-reported measurement when tablet computer technology is used to audio-visually record patients’ responses to health questionnaires on their subsequent ability to recall their previous health status? Secondly, we are assessing whether the provision of previous responses to quality of life questionnaires differs between COPD patients who are enrolled in pulmonary rehabilitation and those who are waiting to commence the program. Thirdly, we will compare the current practice of completing quality of life questionnaires before and after the program. Finally, we will be assessing the feasibility of conducting this study in a busy acute care clinical environment. Our hypothesis is that the magnitude of the difference (responsiveness) between groups of COPD patients will be greatest in those who saw the audio-visual recording.

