#### Eligibility criteria

To be eligible for the study, adults must have a medical diagnosis of COPD and be able to read to year 7 standard to ensure unaided completion of the quality of life questionnaires. Patients with COPD who have significant medical comorbidities that require ongoing acute care will be excluded from participating in the study. Any COPD patient with significant neurological and cognitive impairment such as medically diagnosed dementia will also be excluded. After confirming the patient’s eligibility, study information will be given to patients by the research assistant. Once the patient has had time to review the study information, consent will be sought (Additional file 1). On gaining consent, the patient will be enrolled into an arm of the study and interviewed by the research assistant and data collected. Participants will be re-interviewed 1 month later from the time of their first interview with the research assistant.

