#### Outcomes

There are two outcomes associated with this study; evaluating the feasibility of conducting this study in an acute tertiary admission hospital using the National Institutes for Health Research’s feasibility criteria and testing the hypothesis related to the difference in quality of life indices. The feasibility outcome for this study is the ability to recruit participants who are wait-listed or attending the pulmonary rehabilitation program, administer the interventions in a timely manner and the ease of conducting and completing this study in a busy clinical environment without disruption to the pulmonary rehabilitation service or patient care. The secondary outcome of this randomised controlled trial is concerned with the impact of the patient recall strategies on the quality of life questionnaires’ responsiveness. Specifically, we are measuring the magnitude of statistical difference of quality of life between the three arms of the study.

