#### Sample size

For this pilot randomised control trial and feasibility study, we did not generate a sample size. Thirty (30) adults with COPD, who are either commencing or wait-listed for pulmonary rehabilitation, will be enrolled in this study. The data generated from this study will be used to estimate important parameters that are required to design a larger randomised controlled study to evaluate the role audio-visual recordings using tablet computer technology may play in assisting patient’s recall of their previous health state.

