#### Recruitment

Our pulmonary rehabilitation service is the largest in the health district, which is located on the hospital campus. COPD patients referred to pulmonary rehabilitation can wait up to 6 weeks before commencing the program. All COPD patients, with a referral to or attending the pulmonary rehabilitation program, will be informed about the study and invited to consider participating.

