### Data collection, management and analysis

#### Data collection methods

Consenting, enrolled participants will be assessed at baseline and again 1 month later at the follow-up appointment. The research assistant will record the patient’s demographic information, clinical history, comorbid conditions, medical therapy and past activity and exercise history. The participant will complete the following patient-reported outcome questionnaires at baseline and again 1 month later.European Quality of Life tool that has five dimensions and questions (EQ5D) [19]The Health Survey Short Form with 36 questions (SF36) [20]St Georges Respiratory Questionnaire (SGRQ) [21]Hospital Anxiety and Depression Scale (HADS) [22]

Functional measurements will also be completed at baseline and 1 month later. These include six-minute walk test and lung function testing comprising forced expired volume over 1 s.

Feasibility of conducting this study will be assessed over the course of the study and the following data recorded (Table 1).Willingness of clinicians to refer patients to the studyWillingness of participants to be involved in the studyNumber of eligible patientsCount of participant’s who drop-outFollow-up ratesLength of time to complete recruitment (months)Length of time (min) needed to administration the questionnairesLength of time (weeks) required to complete data analysis

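### Objective 3 promises a before-and-after-programme comparison, but neither visit is tied to the programme, and the rehabilitation group is described as both commencing and already attending

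*Protocol article*

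**What the plan says.** Objectives and hypothesis lists the third aim as "we will compare the current practice of completing quality of life questionnaires before and after the program".

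The visit schedule is set from the research interview. Eligibility criteria states "Participants will be re-interviewed 1 month later from the time of their first interview with the research assistant", and Data collection methods states "Consenting, enrolled participants will be assessed at baseline and again 1 month later at the follow-up appointment". Interventions uses the same 1-month interval. Participant timeline places baseline after consent and enrolment and does not mention the first rehabilitation session. Statistical methods compares mean change over the month between patients who had rehabilitation and those still on the waiting list. This difference is what the article calls responsiveness.

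On who forms the rehabilitation group, Sample size describes the 30 adults as those "who are either commencing or wait-listed for pulmonary rehabilitation". The opening of Methods and Participant timeline also speak of patients commencing. Outcomes, however, defines feasibility as the ability to "recruit participants who are wait-listed or attending the pulmonary rehabilitation program", and Recruitment says that the study will be offered to "All COPD patients, with a referral to or attending the pulmonary rehabilitation program".

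**The concern.** There are two linked problems. First, the objective names time points before and after the programme, while the schedule fixes time points relative to enrolment. Nothing makes the two coincide, and the analysis section contains no comparison across the programme.

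Second, the entry wording differs between sections. A research assistant who follows Recruitment as written could enrol a patient who is part-way through rehabilitation. That patient's first questionnaire is not a pre-programme measurement, and some of any benefit has already accrued.

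At stake is the rehabilitation versus wait-list difference in change, on which the hypothesis about the recall strategies is built. If rehabilitation patients enter at different points, this difference shrinks and depends on the mix of entry times. Sample size says that the data will supply parameters for a larger trial, so an undefined exposure window would carry over into that design. The study is small: if the rehabilitation and wait-list groups are equal (an assumption), 30 patients over 2 groups and 3 strategies is 30/6 = 5 per cell, so a few part-way entrants could shift a cell mean.

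**Working it through.** The plan gives no power calculation, effect size or programme length, so there is no figure of its own to reproduce. The check compares the sections and then shows a range under stated assumptions.

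**Step 1: time points side by side.**
- Objective 3: before and after the programme.
- Visits: enrolment, and 1 month after the first interview.
- Analysis: change over that month.

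For a commencing patient, baseline is approximately before the programme. Whether 1 month is after it depends on programme length *L*, which is not stated. With *T* = 1 month = 4.0 to 4.35 weeks, the share of the programme completed by follow-up is min(*T*, *L*)/*L*: 100% for 4 weeks, 67–72% for 6, 50–54% for 8 and 33–36% for 12. The visit falls after the programme only if the programme lasts no more than about 1 month.

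**Step 2: entry wording side by side.** Commencing: Methods opening, Participant timeline, Sample size. Attending: Outcomes, Recruitment. Eligibility criteria uses neither term, so it does not settle the matter.

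**Step 3: attenuation if attending patients enter.** The yardstick is the 1-month contrast in Statistical methods, with commencing patients exposed for the whole window and wait-list patients not exposed. Assumptions:
- *L* is 4 to 12 weeks.
- Gain is linear in weeks of rehabilitation.
- Time already spent in the programme is uniform on 0 to *L*.

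For *T* ≤ *L*, the mean rehabilitation time in the window for an attending patient is *T* − *T*²/(2*L*).
- *L* = 8, *T* = 4.0: 4.0 − 16/16 = 3.0 weeks, and 3.0/4.0 = 75%.
- *L* = 8, *T* = 4.35: 4.35 − 18.9/16 = 3.17 weeks, and 3.17/4.35 = 73%.

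If a fraction *a* of the rehabilitation group is already attending, the contrast relative to that intended is 1 − *a*(1 − share). At *L* = 8 and *a* = 0.25 this is 1 − 0.25 × 0.25 = 0.94, or 1 − 0.25 × 0.27 = 0.93.

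| Programme length (assumed) | 25% attending | 50% attending | All attending |
|---|---|---|---|
| 4 weeks | 88% | 75% | 50% |
| 6 weeks | 91–92% | 82–83% | 64–67% |
| 8 weeks | 93–94% | 86–88% | 73–75% |
| 12 weeks | 95–96% | 91–92% | 82–83% |

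**Step 4: the wait-list side.** Recruitment gives a wait of up to 6 weeks, longer than the 1-month follow-up. If the remaining wait at enrolment is uniform on 0 to 6 weeks (an assumption), *T*/6 = 67–72% of wait-listed patients would start before follow-up, with mean exposure *T*²/12 = 1.3–1.6 weeks. Analysed by group at enrolment, and with *L* of 6 weeks or more, this alone would cut the contrast to 1 − *T*/12 = 64–67%. Statistical methods may instead intend that starters are excluded or reclassified. This step is therefore a reason to record start dates and does not show a further error.

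**The case against.** The strongest reply is that this is loose wording. The Methods opening and Sample size, which define who is compared and enrolled, say commencing. Recruitment only describes who is told about the study and invited, and Outcomes names the groups in passing. The article is condensed, Figure 1 is not shown, and programme length may be given in a fuller protocol. Feasibility is listed first and responsiveness is called secondary. Allocation is 1:1:1 within both the rehabilitation and wait-list groups, so mixed entry times balance in expectation across the three strategies.

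Much of this stands. The randomisation point limits the harm to the strategy comparison to attenuation and noise, without systematic bias. Loose wording is as plausible as a second entry rule. Even so, the sections disagree on who may enter, and objective 3 does not match the schedule or the analysis printed in the same article.

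A reader might go further and infer that neither time point is delivered and that objective 3 cannot be concluded. The document does not support this. A commencing patient's baseline is approximately pre-programme, and follow-up misses the end only if the programme exceeds about 1 month. The phrase "as part of an 8-week pulmonary rehabilitation intervention" in Background and rationale belongs to a hypothetical study that illustrates recall bias and does not describe this service. Nor is it a fault that wait-listed patients have no post-programme measurement, since they are the comparator by design.

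A reader might also scale the loss against the full effect of an 8-week programme and obtain sample-size factors of 1/0.54² = 3.4 (entry at the start) or 1/0.40², about 6.4 before rounding (uniform entry). Statistical methods promises only a 1-month contrast, so benefit after month 1 lies outside it. Against that contrast the extreme case gives 1/0.73² = 1.9, and there is no sample-size calculation to inflate.

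**Conclusion.** The point holds as a mismatch and an inconsistency. The before-and-after comparison is not assured, because neither visit is tied to the programme, and it differs from the analysis described. The rehabilitation group is defined inconsistently. If attending patients enter, the 1-month rehabilitation versus wait-list contrast is attenuated.

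The document does not give the size. Under an assumed 8-week programme, the attenuation ranges from slight when a quarter of the group is already attending to roughly a quarter of the contrast when all are. A shorter programme makes it worse and a longer one milder. Linear gain and uniform entry are assumptions without support in the text. The correction is worth making before enrolment because it is cheap and fixes what the pilot estimates mean.

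**What to change.** 1. Align Outcomes and Recruitment with the Methods opening, Participant timeline and Sample size: enrol only patients commencing rehabilitation or wait-listed, and require the rehabilitation-group baseline to be completed before the first session.
2. Restate objective 3 as change over the first month of the programme versus 1 month on the waiting list, so that it matches Statistical methods.
3. In both groups, record the date of the first session and the number of sessions attended by follow-up. This lets the exposure within the window be reported, and it shows whether wait-listed patients started before the 1-month visit.

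The cost is a few wording changes and two data fields, with no change to clinical care. The downside is that patients already part-way through cannot be enrolled. Recruitment may then be somewhat slower, which matters because recruitment is itself a feasibility measure; the document gives no figure from which to estimate the delay.

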## Methods

This is a pilot randomised control parallel group trial of three strategies to improve patient recall in the self-report of health status using quality of life questionnaires. These strategies to aid patient recall will be tested in a single centre, randomised controlled trial comparing alternative strategies of assessing change in patient reported outcomes with treatment in an acute care hospital in Australia. The parallel groups comprise COPD patients commencing pulmonary rehabilitation and COPD patients waiting to commence the program. We will compare three strategies to improve patient recall with the standard approach of patient’s completing the questionnaires at each study time point. These new strategies in addition to current practice are (1) the use of tablet technology’s audio-visual functionality and (2) the provision of patient access to their baseline questionnaire responses prior to completion of questionnaires at follow-up. Additionally, we are assessing the feasibility of using these patient strategies to improve patient recall when completing self-report PROs questionnaires in a busy acute care hospital. Feasibility will be assessed according to the National Institute for Health Research (NIHR) feasibility study criteria (Table 1) [18].

**Table 1 Tab1:** Feasibility assessment for recall study

Feasibility item	Record
Willingness of clinicians to refer patients to the study	Number of referrals to study
Willingness of participants to be involved in the study	Number of patients approached but chose not to participate
Number of eligible patients	Number of patient who are eligible based on criteria
Number of participants that dropped out of study	Number of participants who withdrew and reasons or died
Follow-up rates	Number of participants who completed time 2 questionnaires
Length of time to complete recruitment of participants	Time in months
Length of time to administer intervention	Time in minutes
Length of time to analyse data	Time in days

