**Fig. 1 Fig1:**
[figure not shown]
Study participant numbers in each group and study interventions protocol

Clinical care will not be affected and the clinical team will continue the medical management of the patient during the timeframe of the study. The investigator team members are not part of the clinical or pulmonary rehabilitation teams. Patients who become clinically unwell and unable to attend the follow-up appointment will be included in the analysis.

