### Assignment of interventions

#### Allocation

For this pilot study, participants will be allocated to one of three recall strategies; tablet technology audio-visual recording, reviewing their previous responses or standard practice (Fig. 1).

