#### Sequence generation

Eligible participants will be randomised 1:1:1 assigned ratio to one of the three intervention arms in both the pulmonary rehabilitation and wait list groups using the computer-generated randomisation code.

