#### Statistical methods

Demographic and clinical information will be assessed using descriptive statistics measuring frequencies, means and standard deviations. We will measure the within-subject change in PRO questionnaire scores over the 1-month period. The difference in mean change between those who had pulmonary rehabilitation and those who remained on the waiting list over this 1-month period will be calculated. Finally, the magnitude of this difference (responsiveness) of these scores will be compared between groups. Our hypothesis is that the magnitude of the difference (responsiveness) will be greatest in those who saw the audio-visual recording.

Feasibility will be reported using descriptive statistics such as frequencies, rate, means and standard deviations to interpret whether it is feasible to conduct a larger study in this busy clinical environment.

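### Responsiveness is defined by a rehabilitation-versus-wait-list difference that is not randomised, so its absolute size is an observational estimate and should be analysed and labelled as one

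*Protocol article*

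**What the plan says.** The opening of Methods calls the study a pilot randomised parallel-group trial and then identifies the groups: "The parallel groups comprise COPD patients commencing pulmonary rehabilitation and COPD patients waiting to commence the program".

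The allocation sections describe a different factor. Under Allocation, "participants will be allocated to one of three recall strategies; tablet technology audio-visual recording, reviewing their previous responses or standard practice". Under Sequence generation, the 1:1:1 randomisation gives each eligible patient "one of the three intervention arms in both the pulmonary rehabilitation and wait list groups". No section randomises, matches or balances patients between rehabilitation and the wait list. That status is the patient's place in the service at enrolment.

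Statistical methods builds the outcome in two steps. First, "The difference in mean change between those who had pulmonary rehabilitation and those who remained on the waiting list" over the month is calculated. Then "the magnitude of this difference (responsiveness) of these scores will be compared between groups". No adjustment for baseline status is named.

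Objectives and hypothesis adds a second objective that compares rehabilitation with waiting patients directly, among those given their previous responses. It also states the hypothesis that responsiveness is greatest with the audio-visual recording. Sample size says that the data will supply parameters for a larger trial.

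**The concern.** The words randomised and parallel group are attached to a factor that is not randomised, and the difference across that factor is the building block of the outcome. A reader of the results could take a responsiveness figure as a randomised estimate of how strongly a questionnaire registers the effect of rehabilitation. It is an observational contrast between patients at two stages of a care pathway. Ordinary care also goes on in both groups: "the clinical team will continue the medical management of the patient during the timeframe of the study" (Interventions, text after Fig. 1).

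Three things are at stake:

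- the absolute responsiveness reported for each strategy;
- the second objective, which is wholly a rehabilitation-versus-waiting comparison;
- the planning parameters taken into a larger trial.

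**Working it through.** The plan states no power or effect figure, so there is nothing to reproduce. The check is on what the stated outcome estimates.

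**Inputs from the protocol.** Strategy is randomised 1:1:1 within each clinical group (Sequence generation). Responsiveness is mean change in rehabilitation minus mean change on the wait list (Statistical methods). Total enrolment is 30 (Sample size).

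**Assumptions, not in the protocol.** All values are in units of the SD of the change score. The rehabilitation effect is τ = 0.5. The difference between the two groups in natural course or case mix is b, tried at 0, 0.3 and 0.5, and at −0.3 because its direction is unknown. Strategy k multiplies reported change by g_k, with g = 1 for standard practice and g = 1 or 1.5 for the audio-visual strategy. Equal cells give 30/(2 × 3) = 5 patients each (Fig. 1 was not available).

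**Step 1: what each responsiveness figure estimates.** Let the change without rehabilitation be m_R in rehabilitation patients and m_W in waiting patients, so b = m_R − m_W. Under strategy k the mean reported changes are g_k(τ + m_R) and g_k·m_W, and

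R_k = g_k(τ + m_R) − g_k·m_W = g_k(τ + b).

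The whole of b is read as response to rehabilitation.

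**Step 2: what the comparison between strategies estimates.** R_k − R_j = (g_k − g_j)(τ + b). If no strategy has an effect, g_k = g_j and the difference is 0 for every b. A strategy that adds the same constant to both clinical groups also cancels. Only when a strategy scales reported change does b enter.

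| b | Standard practice: 0.5 + b | Audio-visual, g = 1.5: 1.5 × (0.5 + b) | Difference: 0.5 × (0.5 + b) |
|---|---|---|---|
| −0.3 | 0.20 | 0.30 | 0.10 |
| 0 | 0.50 | 0.75 | 0.25 |
| 0.3 | 0.80 | 1.20 | 0.40 |
| 0.5 | 1.00 | 1.50 | 0.50 |

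A simulation of 200,000 runs with 5 per cell, for b = 0, 0.3 and 0.5, gave the same means to within 0.004. With g = 1 in both arms, the simulated between-strategy difference was 0.00 at each b.

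**Step 3: sampling error, for scale.** With 5 per cell, SE(R_k) = √(2/5) = 0.63 SD, so the 95% half-width is 1.96 × 0.632 = 1.24 SD. For two strategies, SE(R_k − R_j) = √(4/5) = 0.89 SD, half-width 1.75 SD. These figures measure imprecision, which randomising rehabilitation would not remove. They are not a measure of confounding.

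**Step 4: what randomisation does protect.** Between strategies, the contrast is (g_k − g_j)(τ + m_R) among rehabilitation patients and (g_k − g_j)·m_W among waiting patients. Each compares randomised patients. The difference in responsiveness is the first minus the second, so reporting both shows where it comes from.

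**The case against.** The strongest reply is that the hypothesis concerns recall strategies, not the effect of rehabilitation, and strategy is randomised to "one of the three intervention arms in both the pulmonary rehabilitation and wait list groups". Differences between the clinical groups are then common to all three arms. This stands for the test of no strategy effect (Step 2). It does not cover absolute responsiveness, the second objective, or the size of a strategy effect that works by scaling. The hypothesis is about magnitude, so scaling is a natural form for the effect to take.

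It can also be said that Methods never claims that patients are randomised to rehabilitation, and that the allocation sections make the position clear. That is fair: the fault there is loose wording. Covariates are often left to an analysis plan, but Statistical methods does fix the outcome as a difference in mean change, and that statement can be improved where it stands.

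Several stronger readings are tempting, and the protocol does not support them:

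- **That the strategies cannot be told apart.** Randomisation within each group protects that comparison when there is no effect. Otherwise confounding alters its size and does not in general abolish it.
- **That waiting patients enter soon after referral and are still recovering.** Participant timeline gives no timing of approach. The six weeks under Recruitment is a maximum wait, not a measured gap between the groups.
- **That medical therapy is recorded only at baseline.** The sentence in Data collection methods follows one that names both visits and does not restrict collection to the first.
- **That wait-list improvement, or chance baseline imbalance in cells of about five, measures the confounding.** A randomised wait list would show both.
- **That leaving out patients with an exacerbation or therapy change during follow-up would be a useful check.** It conditions on events after randomisation and thins very small cells.

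**Conclusion.** The concern holds in limited form. Each strategy's absolute responsiveness and the second objective rest on a non-randomised contrast that Methods presents as the parallel groups of a randomised trial. The bias equals whatever difference in case mix or natural course exists between the groups. The protocol neither shows that such a difference exists nor allows its size or direction to be derived.

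The SD figures depend on the assumed τ, b and g and are illustrations, not predictions. At the assumed cell size, the biases tried are smaller than the sampling error of any one estimate in this pilot. Unlike sampling error, though, such a bias would not shrink in a larger trial built in the same way. The point bears on a secondary outcome of a 30-patient pilot. It is worth correcting because the correction is cheap and the estimates are meant for planning.

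**What to change.** 1. In Methods and Statistical methods, state that only the recall strategies are randomised and that the rehabilitation-minus-wait-list difference is observational.
2. Estimate responsiveness from one model per questionnaire: follow-up score on strategy, clinical group and their interaction, adjusted for the baseline score of the same questionnaire. The group difference within each strategy is that strategy's responsiveness, and the interaction terms compare strategies. Show the unadjusted difference in change beside it. The clinical groups are not randomised, so the adjusted and unadjusted analyses can differ systematically, and neither is free of confounding. Tabulate baseline six-minute walk distance and FEV1 by clinical group.
3. Report the randomised between-strategy contrasts within the rehabilitation group and within the wait-list group, next to the difference, so that change on the wait list is seen as well as subtracted.

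Cost: all the data are already planned. The covariate takes one degree of freedom. With six cells and all 30 patients followed, residual degrees of freedom fall from 30 − 6 = 24 to 23. The rehabilitation difference also carries a weaker label. Allocation and clinical care do not change.
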